## Methods

This trial protocol was developed in accordance with the Consolidated Standards of Reporting Trials (CONSORT) and the Standard Protocol Items: Recommendations for Interventional Trials (SPIRIT) 2013 Statement [68, 69]. For the SPIRIT checklist, see supplement S1.

### Service user involvement

Two service users and two therapists tested a first version of “Goals in Focus” before this pilot trial and provided feedback on the intervention. The adaptations suggested by the service users were to switch the order of instruments within the assessment phase and to start with the biographical anamnesis, followed by the situational analyses. These suggestions were discussed with the research team and implemented in the current version of “Goals in Focus”. For the current trial, a qualitative user survey will be used at the end of treatment to collect participants’ suggestions for improvement of “Goals in Focus”.

### Study design

The study is conducted as a single-blind, parallel-group, randomized wait-list controlled feasibility trial (see Fig. 1 for study plan and assessment schedule) implemented at the psychology outpatient clinic at Universität Hamburg. The trial received approval from the ethics committee of the chamber of psychotherapists Hamburg (03/2020-PTK-HH) and has been preregistered at ClinicalTrials.gov (Identifier: NCT05252039) and Deutsches Register Klinischer Studien (Identifier: DRKS00018083). Any modifications to the protocol will be logged using these identifiers and, if required, will be communicated with the participants and secured by amendments to ethical approval. Outcomes will be measured at baseline (*t*_0_) and 6 months after baseline assessment (*t*_1_). Table 1 provides an overview of the trial design and assessment instruments. Recruitment started in 2020 and is planned to terminate in autumn 2023.

**Table 1 Tab1:**
[figure not shown]
Schedule of enrolment, interventions, and measures at baseline- and 6-months-assessment (SPIRIT guidelines, 2013) [62, 63]

*BNSS* Brief Negative Syndrome Scale, *RFS* Role Functioning Scale, *GAF* Global Assessment of Functioning Scale, *WEMWBS* Warwick–Edinburgh Mental Well-Being Scale, *CDSS* Calgary Depression Rating Scale for Schizophrenia, *SCID* Structured Clinical Interview for DSM-5, *PSYRATS* Psychotic Symptoms Rating Scales

**Fig. 1 Fig1:**
[figure not shown]
Trial flow diagram

### Participants

#### Eligibility criteria

Eligible participants: (1) meet a diagnosis of a schizophrenia spectrum disorder (confirmed by the Structured Clinical Interview for DSM-5 Clinical Version (SCID-5-CV [70], German version [71]); (2) report at least moderate motivational negative symptoms, i.e., scores ≥ 3 (“moderate”) in two items or ≥ 4 ( “moderately severe”) in one item of the “motivation and pleasure factor” of the Brief Negative Symptom Scale (BNSS) [72, 73]—cut-off criterion was selected based on previous studies with comparable design [18, 74]; (3) be aged between 16 and 85 years; (4) have sufficient skills in German language to participate in psychological therapy (no requirement to speak German fluently); (5) be able to engage in weekly therapy sessions of 50 min; (6) prioritize the reduction of negative symptoms as their current goal for treatment, and (7) be able to give informed consent to participate in the trial. Participants are excluded if they (1) are an immediate and serious risk of harm to themselves or others; (2) have a comorbid diagnosis of alcohol or substance use disorder; (3) report intake of Benzodiazepines for >2 days per week (given that potential side-effects, such as drowsiness and affect motivation), or (4) currently receive any other therapy for motivational negative symptoms.

#### Recruitment, randomization, and blinding

Participants are recruited from outpatient settings in Hamburg (i.e., clinical psychologists and psychiatrists in private practice, social services), psychiatric clinics, and local self-help groups. Participants are either referred to the study by practitioners or via self-referral.

Enrolled and potentially eligible participants are invited for a study information meeting with a trial therapist. The participant will receive a copy of the participant information sheet which provides detailed information about the aims of the study and trial procedures. Participants are given the opportunity to ask questions. Following the information meeting, participants have sufficient time (24 h to 1 week) to consider their participation. After providing informed consent, participants meet with a trial rater who assesses eligibility and completes the baseline assessment with eligible participants. Clinical interviews are conducted by trial raters (psychologists in clinical training with at least master’s degree). All raters have already undergone training in basic therapeutic skills, such as assessment and building rapport. All raters receive a 4-h rater training by the trial manager on all of the observer-rated measures used in this trial. Allocation to either treatment- or wait-list control group is conducted (1:1) using permuted blocks of 4, 6, and 10 to reduce predictability of the sequence. The randomization schedule is generated and preserved by an assistant of the work group who is not otherwise involved in trial procedures. The trial manager is informed about the participant’s group allocation and notifies the participant and the responsible trial therapist.

Blinding of participants is not possible due to the nature of this study. Because trial raters work in the same facilities as trial therapists (i.e., they attend weekly team meetings, meet patients on the hallway, etc.), they also cannot be reliably blinded. Therefore, each assessment is video-recorded and rated by an independent second rater blinded to group allocation and time of assessment. At the beginning of each assessment, participants are reminded to not disclose their group allocation. Video sequences that could reveal the participant’s allocation or point of assessment are deleted before the secondary rating. Secondary raters are asked to record any breaks of blinding, even if the break is equivocal. Putatively unblinded raters are asked to guess the allocation group for the respective participant. Confirmed breaks in blinding of raters follow a standard operating procedure to maintain blind outcome assessments by reallocating “blind” raters for the respective secondary rating, therefore not biasing results.

#### Sample size

An a priori power calculation is not appropriate for this feasibility trial as the study aim is not to test efficacy. Nonetheless, we aim to examine first effect size estimates of “Goals in Focus” on our primary and secondary outcomes. These estimates will inform the sample size calculation for a future fully powered RCT. Based on the recommendations for feasibility studies [75] and on existing feasibility trials in this field [76, 77], the target for this feasibility study was set at *N* = 30 participants (*n* = 15 intervention group; *n* = 15 wait-list control group).

### Interventions

#### Explanation for the choice of comparators

A two-arm, randomized wait-list controlled design was chosen to control for spontaneous remission and to test whether “Goals in Focus” is superior to wait-list control in reducing motivational negative symptoms in patients with psychosis.

#### Wait-list control group

Participants randomized to the “wait-list control group” will be contacted again after 6 months for post-assessment and then offered the “Goals in Focus” intervention. These participants will also be informed that they may use other pharmacological or psychosocial mental health care services but are asked to refrain from psychological interventions that directly target motivational negative symptoms. At the end of the wait-list period, participants in this condition are asked to provide information on any inpatient or outpatient treatment they have received and on major events they consider to have influenced their symptoms during this period.

#### Goals in Focus

Participants randomized to the “intervention group” will receive up to 24 weekly 50-min sessions of “Goals in Focus” within the following 6 months. The main components of “Goals in Focus” were selected based on basic research [21] and existing therapy approaches on motivational negative symptoms [47, 66, 74, 78]. They were then combined to a customized and readily conveyable manualized approach. “Goals in Focus” follows cognitive–behavioral principles and aims to alleviate motivational negative symptoms by improving goal pursuit. The intervention is delivered in a one-to-one setting by clinical psychologists (master’s degree plus advanced or completed clinical training). All trial therapists receive an additional 2-day training in using the treatment manual, including background information on the rational of “Goals in Focus” and a step-by-step introduction to the individual intervention components. Trial therapists are offered weekly supervision by a senior expert on cognitive behavior therapy for psychosis and are requested to attend at least once per month to increase adherence to the treatment manual. “Goals in Focus” comprises four main phases: (1) preparation, (2) goal setting, (3) supported goal pursuit, and (4) working towards autonomous goal pursuit. An overview on the structure and sequence of “Goals in Focus” intervention is presented in Fig. 2, a table on the domains and intervention elements of “Goals in Focus” is provided in supplement S2.

**Fig. 2 Fig2:**
[figure not shown]
Structure and sequence of “Goals in Focus” intervention

##### Phase 1, preparation (sessions 1–6)

The aim of phase 1 is to develop an individual case formulation with a focus on the motivational negative symptoms and to collaboratively deduce an individualized treatment plan building on previous experiences of successful and unsuccessful goal pursuit.

##### Phase 2, goal setting (sessions 7–8)

The aim of phase 2 is for participants to set personally valuable goals and to identify first steps towards goal realization. Participants are asked to complete an activity log over the course of 1 week which is used to identify goals that are already being pursued. Next, participants are introduced to different domains of goals (social, recreational, occupational, and health goals) and are asked to select at least one personally meaningful goal related to each of the goal domains. This is complemented by psychoeducation on functional goal setting (e.g., formulating approach goals rather than avoidance goals or cutting long-term goals down into preceding steps of middle- and short term-goals), encouraging patients to adapt these principles to their goals.

##### Phase 3, supported goal pursuit (sessions 9–22)

The goal pursuit phase comprises four consecutive modules of interventions to increase the participants’ goal pursuit. These include (a) increasing the salience of rewards, (b) training anticipatory pleasure, (c) challenging demotivating beliefs, and (d) facilitating social and problem-solving skills. In this phase, the patient is encouraged to set goals that are achievable within 1 week, i.e., until the next session. Aiming to support the pursuit and the achievement of these goals, module a) focuses on reward-processing aiming to improve the representation of the rewards and positive experiences associated with reaching next weeks’ goals. Module b) focuses on improving the anticipation of pleasure with regard to the respective goal by using mental imagery of positive experiences. Module c) focuses on identifying and altering demotivating beliefs that discourage goal pursuit by using cognitive interventions, such as Socratic dialogue or behavioral experiments. Module d) focuses on improving the specific social- and problem-solving skills and aims to build or increase these skills as required for the realization of next week’s goal (e.g., practicing small talk in role play with the therapist in order to accomplish the goal “start a conversation with my neighbor”). Together, participants and trial therapists agree on which of the modules a) to d) will be implemented according to participants’ individual goals and individual problems in goal pursuit.

##### Phase 4, working towards autonomous goal pursuit (sessions 23–24)

The aim of the final phase is to reflect on effective strategies and to prepare for challenges in goal pursuit after therapy termination. Initially set phase 2 goals and the respective goal progress are revised, helpful strategies for goal pursuit are identified and rehearsed, and plans for prospectively pursuing the established or new goals are made.

### Outcomes

#### Feasibility and acceptability measures

To assess feasibility of “Goals in Focus” and trial procedures, the following data is collected: (1) referrals (number of participants referred to the study), (2) eligibility rates (proportion of enrolled participants found eligible), (3) number of participants consenting to study participation and reasons for refusals, (4) retention rate (i.e., number and proportion of participants who attend *t*_1_ assessment and completeness of data at *t*_1_), (5) attendance rates and dose of intervention (i.e., number of sessions delivered within 6 months), (6) data attrition (proportion of outcome data not obtained), and (7) treatment adherence as indicated by the therapists’ self-report in the post-treatment questionnaire.

Acceptability is assessed by (1) drop-out rate (i.e., number of withdrawals), (2) number of adverse events, (3) participants’ satisfaction with treatment and personal outcomes and suggestions for improvement as indicated by each participants’ response to three quantitative and three qualitative questions (see post-intervention questionnaire, supplement S 3; e.g., participants are asked to indicate how helpful they perceived “Goals in Focus” to be for their problems and for approaching their goals and to suggest improvements), and (4) therapists’ satisfaction as measured by the post-intervention questionnaire, therapist version (see supplement S 4).

Progression criteria for a subsequent trial were set according to existing recommendations for feasibility studies [79, 80] and can be found in Table 2.

**Table 2. Tab2:**
[figure not shown]
Progression criteria

#### Primary clinical outcome

The primary outcome for effect size estimation is measured with the baseline-adjusted “motivation and pleasure factor” (i.e., sum score of the seven items of this factor) of the Brief Negative Symptoms Scale (BNSS) at *t*_1_ [72, 73]. The BNSS is a 13-item semi-structured interview measuring negative symptoms on two factors, namely “motivation and pleasure” and “reduced expressivity” [81]. The “motivation and pleasure factor” includes seven items that measure the subscales of “anhedonia,” “avolition,” and “asociality” [82]. Symptoms are rated on a 7-point scale ranging from 0 “no impairment” to 6 “severe deficit”.

#### Secondary clinical outcomes

Specific facets of negative symptoms are assessed according to the five-factor model of negative symptoms [83]. This includes the three subscales avolition, asociality, and anhedonia of the BNSS “motivation and pleasure factor” and the two subscales blunted affect and alogia of the BNSS “reduced expressivity factor”.

Psychosocial functioning is assessed using the Role Functioning Scale (RFS) [84] and the Global Assessment of Functioning (GAF) [85]. The RFS is a semi-structured interview and assesses four domains of functioning on the subscales “working productivity,” “independent living,” “immediate social network,” and “extended social network”. Participants’ answers are rated with regard to anchor points, ranging from 1 “low functioning” to 7 “optimal functioning”. For subsequent analyses, a mean score for total functioning will be calculated. The GAF [85] is used as an observer rating of psychosocial functioning. Functioning is rated on a single scale ranging from 1 (lowest) to 100 (highest) based on detailed anchor points.

Subjective well-being is assessed with the Warwick–Edinburgh Mental Well-Being Scale (WEMWBS) [86, 87]. The WEMBS is a self-report questionnaire consisting of 14 statements on well-being during the previous 2 weeks (e.g., “I’ve been feeling good about myself.”). Participants rate these items on a 5-point Likert scale ranging from 1 (“none of the time”) to 5 (“all of the time”).

Symptoms of depression are assessed with the Calgary Depression Rating Scale for Schizophrenia (CDSS) [88, 89]. The CDSS is a 9-item semi-structured interview which has been developed to measure depressive symptoms in patients with schizophrenia. The participant’s answers are rated by the interviewer on a 4-point scale referring to explicit anchor annotations ranging from 0 (“clearly absent”) to 3 (“severe”).

Goal pursuit in daily life is assessed using ecological momentary assessment (EMA). The EMA protocol can be seen in Fig. 3. Participants will be prompted twice a day (10 a.m. and 10 p.m.) over the course of 1 week via the Movisens XS application (Movisens GmbH) installed on smartphone devices provided by the research team. At the beginning, the participants’ self-efficacy is assessed with the Generalized Self-Efficacy Scale (GSE) [90]. Each of the following “10 a.m. prompts” asks the participants to nominate a goal they would like to achieve during the respective day and to rate characteristics of this goal (e.g., goal commitment, goal importance, goal difficulty, etc.). At the “10 p.m. prompts,” participants are asked to indicate to what extent they achieved the respective goal and to answer questions on their causal attributions and affective experience regarding their goal pursuit.

**Fig. 3 Fig3:**
[figure not shown]
Ecological momentary assessment of goal pursuit in daily life

#### Additional measures

Participants are asked to provide sociodemographic and clinical information (e.g., age, gender, living situation, occupational status, as well as psychiatric history, medication) at baseline. Any changes in medication, occupational status, living situation, or adjunct treatments between *t*_0_ and *t*_1_ are recorded throughout the trial. The severity of positive symptoms is assessed at *t*_0_ and *t*_1_ with the Psychotic Symptom Rating Scales (PSYRATS) [91, 92] to be able to control for a possible confounding influence of reduced positive symptoms on changes in negative symptoms.

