#### Analysis plan

Feasibility and acceptability will be analyzed by calculating descriptive statistics based on the intention-to-treat (ITT) population. Potential reasons for trial withdrawal will be examined by comparing baseline characteristics (e.g., symptom severity, sociodemographic variables, etc.) between participants who completed the trial and participants who discontinued their participation after randomization.

Clinical outcomes at baseline assessment (*t*_0_) and 6-month assessment (*t*_1_) will be summarized using descriptive statistics (i.e., frequency and percentages on binary and categorical variables; means, standard deviations, or medians, with minimum and maximum values for continuous variables) for each arm of the trial separately. Wait-list control and treatment group characteristics at baseline will be compared using Pearson chi-square tests for the categorical variables and the *t*-test or Mann–Whitney test for the quantitative variables.

Confirmatory analysis will be conducted for primary and secondary outcomes based on the ITT population. An ANCOVA adjusted for baseline values will be calculated with group allocation as between-subject factor and time as within-subject factor. Any variables that show significant group differences at baseline or are found to correlate with the primary outcome (e.g., age, gender, diagnosis, medication doses, duration of illness, symptom severity, etc.) will be entered as covariates. Effect sizes between and within treatment conditions will be assessed by calculating Cohen’s *d*. Missing values will be handled by multiple imputation, if missing completely at random [93]. All analyses will be carried out using validated statistical software.

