“Goals in Focus” was developed to directly target the relevant motivational negative symptom domains by translating recent empirical research on factors and mechanisms underlying motivational negative symptoms into specified interventions. The comprehensive treatment approach is tested in a randomized controlled trial design which allows to eliminate a possible selection bias and to control for spontaneous remission effects. However, there are some limitations to our study design: this is a pilot trial with the main focus on feasibility and the sample of 30 participants is not sufficient for a reliable efficacy analysis. As likelihood of type 1 error inflation is high, results of significance tests cannot be interpreted, but effect sizes derived from the present study will be used for a priori sample size calculation for a subsequent fully powered RCT. The advantage of a wait-list control condition is that it allows a first estimation of effects and enables wait-list participants to later receive the same intervention. Also, diffusion effects between the conditions (e.g., patients from the wait-list group receiving information about the intervention from other patients, therapists including intervention elements in standard treatment) are unlikely due to the outpatient setting and the fact that treatment as usual is not provided by trial therapists. A disadvantage is that the wait-list comparator may artificially inflate estimates of the intervention effect, due to participants being held in a waiting position and less likely to initiate behavioral change on their own (e.g., as suggested by Cunningham et al. [94]). Additionally, the eligibility criterium of “being able to engage in weekly therapy sessions of 50 min” limits the generalization of effects to those who are not able to attend weekly sessions for the full-time range of 50 min. Other issues that warrant mention relate to the selected outcomes: since “Goals in Focus” aims at improving goal setting and achievement, the EMA of goal pursuit is of particular interest. However, participants’ adherence to an autonomously conducted 1-week survey might be reduced, which is why we did not select it as the primary outcome. Also, a long-term follow-up was not included at this point due to the primary focus being on acceptability, feasibility, and first estimates of efficacy. It also needs to be kept in mind, that the intervention only targets motivational negative symptoms and not expressive negative symptoms, the other relevant component of negative symptoms [72, 95]. However, we expect expressive negative symptoms to be indirectly affected by the intervention as suggested by results reported by Choi et al. [18] in relation to a similar treatment approach. Accordingly, expressive negative symptoms are evaluated as a secondary outcome. Similarly, the intervention does not target contextual factors, such as social deprivation or health-related issues that are likely to exacerbate negative symptoms, but expect the achievement of personal goals due to the intervention to partially improve participants’ challenging contextual factors as well.

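### The plan gives control of a post-randomisation fall in positive symptoms as a purpose, and its covariate rule is not limited to baseline values, so the planning effect size could be adjusted for a possible mediator.

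*Protocol article*

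**What the plan says.** Under Additional measures, the article says of PSYRATS: "The severity of positive symptoms is assessed at" baseline and 6 months, and gives the reason: "to be able to control for a possible confounding influence of reduced positive symptoms on changes in negative symptoms". The quantity to be controlled is a reduction, which cannot be computed without the 6-month value.

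In Recruitment, randomization, and blinding, the baseline assessment is described before allocation: "Allocation to either treatment- or wait-list control group is conducted (1:1) using permuted blocks of 4, 6, and 10". Study design places the second assessment 6 months after baseline.

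The primary outcome section states: "The primary outcome for effect size estimation is measured with the baseline-adjusted “motivation and pleasure factor" score at 6 months. The Analysis plan has the matching model: "An ANCOVA adjusted for baseline values will be calculated with group allocation as between-subject factor and time as within-subject factor". It then adds covariates by two routes: a significant group difference at baseline, or variables that "or are found to correlate with the primary outcome". The examples are given as "e.g., age, gender, diagnosis, medication doses, duration of illness, symptom severity, etc.) will be entered as covariates". PSYRATS is not named there, and neither is any change score.

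The Discussion says what the estimate is for: "effect sizes derived from the present study will be used for a priori sample size calculation for a subsequent fully powered RCT".

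**The concern.** In a randomised comparison, a confounder must precede allocation or at least not result from it. A change in positive symptoms during the 6 months after allocation does not qualify. It may be produced by the therapy, in which case it is a mediator. It may also share unmeasured causes with the negative-symptom outcome, in which case conditioning on it opens a path that randomisation had closed. Either way, the adjusted contrast is a kind of direct effect that randomisation does not protect, rather than the total effect by intention to treat.

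The adjustment is also not needed for the reason the article gives. Its section on the choice of comparator says the wait-list arm is there to control for spontaneous remission. Background falls in positive symptoms are therefore balanced in expectation already. Systematic differences that open up after allocation are part of the total effect.

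What is at stake is the planning value. The trial is not meant to test efficacy, but its between-arm effect size is to set the sample size of the next trial. An effect adjusted for a consequence of treatment answers a different question from the one that trial will ask.

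**Working it through.** **No figure in the plan depends on this point.** The 30 participants come from feasibility recommendations, not from a formula, so there is nothing to reproduce. The calculation below only illustrates size, and all its inputs are assumptions.

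**Inputs (assumed):**
- total effect on negative symptoms, *d*_neg = 0.50 SD;
- effect of therapy on the reduction in positive symptoms, *d*_pos = 0, 0.2 or 0.5 SD;
- within-arm correlation between positive-symptom change and the outcome, ρ = 0.3 or 0.5;
- for the later trial, two-sided 5% and 80% power.

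**Formulas.** With both variables on a unit-SD scale and effects signed as benefit:
- adjusted difference = *d*_neg − ρ × *d*_pos;
- n per arm = 2 × (1.960 + 0.842)² / *d*² ≈ 15.70 / *d*² (normal approximation).

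| *d*_pos | ρ | Adjusted difference | n per arm it would imply |
|---|---|---|---|
| 0 | any | 0.50 | 63 |
| 0.2 | 0.3 | 0.50 − 0.06 = 0.44 | 82 |
| 0.2 | 0.5 | 0.50 − 0.10 = 0.40 | 99 |
| 0.5 | 0.3 | 0.50 − 0.15 = 0.35 | 129 |
| 0.5 | 0.5 | 0.50 − 0.25 = 0.25 | 252 |

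Using the t distribution adds about one per arm (64, 83 and 253 for differences of 0.50, 0.44 and 0.25).

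**Simulation check.** With 15 per arm and 4,000 runs per scenario, the model without the change score returned 0.49 to 0.51 throughout. With the change score it gave 0.498 (*d*_pos = 0, ρ = 0.3), 0.447 (0.2, 0.3) and 0.244 (0.5, 0.5), in line with the formula.

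**No mediation is needed for bias.** Suppose positive-symptom change has no effect on the outcome, but an unmeasured cause loads 0.5 on both. The slope is then 0.5 × 0.5 = 0.25. The adjusted difference is 0.50 − 0.2 × 0.25 = 0.45, or 0.50 − 0.5 × 0.25 = 0.375 (simulated: 0.447 and 0.38).

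**Scaling.** The table divides by the unadjusted SD. If *d* were instead standardised by the residual SD of the adjusted model, √(1 − ρ²), the 0.44 becomes 0.44 / √0.91 = 0.461 and the 0.25 becomes 0.25 / √0.75 = 0.289. These imply about 74 and 189 per arm (75 and 190 with the t distribution).

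**Direction.** If positive symptoms improve less under therapy than on the wait list, *d*_pos is negative and the adjusted difference exceeds 0.50. Wait-list participants may use other pharmacological or psychosocial care, so this cannot be excluded.

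**The case against.** The strongest reply is that the plan does not commit to this adjustment. A reader might infer that the primary model will contain PSYRATS change. The documents do not support that. The wording under Additional measures gives a reason for collecting a measure, the Analysis plan never names PSYRATS, and the primary outcome is defined as corrected for baseline only. A supportive or explanatory use would fit the text too. This stands, and it limits the point to a wrong rationale beside a rule that does not keep the variable out.

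A reader might also infer that listing symptom severity and medication doses deliberately lets in follow-up values. That reading is too strong. The same section uses symptom severity as an example of a baseline characteristic, and age, gender, diagnosis and duration of illness are naturally baseline variables. Only the second route, correlation with the outcome, is grammatically open.

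Nor can one say that the planning *d* will be biased. The Analysis plan does not say that Cohen's *d* is taken from the covariate-extended model. There is also no bias in expectation if therapy leaves positive symptoms alone. The Phase 3 modules address reward, anticipatory pleasure, demotivating beliefs and skills, and none is directed at positive symptoms.

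The illustrated shift is small beside sampling error. With 15 per arm, the standard error of *d* = 0.50 is √(2/15 + 0.25/60) ≈ 0.37, and the Discussion already concedes that the sample cannot support a reliable efficacy analysis. That is fair, but imprecision does not excuse an avoidable change of estimand.

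Finally, asking how far negative symptoms improve only because positive symptoms do is legitimate, and positive-symptom change can offer a rival explanation of within-arm change. The article does not confine the control to either use or label it as such.

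**Conclusion.** The point holds in a limited form. The article treats a post-randomisation reduction in positive symptoms as a possible confounder, which it cannot be for the randomised comparison. The correlation route of the covariate rule would not exclude it. If it were entered, and if therapy affects positive symptoms, the between-arm estimate would no longer be the intention-to-treat effect needed for planning.

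The size is unknown because the documents supply no inputs. Under the stated assumptions, the adjusted difference lies between 0.50 SD (no bias) and 0.25 SD. The lower end is a worst case, and the sample sizes derived from it depend further on which SD is used for scaling. None of these figures predicts what the trial will find. The matter is worth correcting because the remedy is simple and protects one of the trial's main products.

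**What to change.** In the Analysis plan, limit covariates in the effect-size model to variables measured at baseline. Baseline PSYRATS may be one of them, in the main model or in a sensitivity analysis.

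Under Additional measures, replace the confounding rationale with a statement that PSYRATS change is reported by arm as an outcome and is not entered in the effect-size model. Add that any analysis adjusting for it is exploratory mediation and labelled as such.

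The cost is a few sentences. The baseline and 6-month PSYRATS data are already part of the schedule, so no assessment changes.
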